**Conclusion::**

This is the first human intervention study to investigate the cholesterol-lowering effects and safety of yellow yeast rice in adults with mild to moderate hypercholesterolemia. Also, this is a randomized, double-blind, placebo-controlled trial that considers confounders, such as dietary habits, lifestyle factors, and genetic factors.

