### Randomization, allocation concealment, and blinding

2.4

Randomization sequence is computer generated by an independent statistician. All the labeled test and placebo products are provided by Daesang Co, Ltd (Seoul, South Korea). The randomization numbers are kept in opaque sealed envelopes. Group assignments are not revealed and are blinded to the participants and investigators throughout the entire study. The participants who meet the eligibility criteria are randomly assigned (1:1) to either receiving either placebo or yellow-yeast-rice-treated group. Randomization is stratified by gender. Allocation concealment is maintained since no sealed envelope is opened during the study.

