**Table 1 T1:**
[figure not shown]
Schedule of data collection.

Outcomes related to effectiveness and safety, as well as possible covariables, including demographic information, anthropometric measures, dietary habits, physical activity, alcohol consumption, and smoking behavior, will be assessed. Face-to-face interviews will take place at the first screening, baseline, 4 weeks, and 8 weeks after intervention. Possible covariables will be surveyed using structured questionnaires.

Standardized interviews and blood sampling will be carried out by trained investigators and research coordinators. Participants will be instructed to arrive for laboratory testing between 8:30 am and 9:30 am after a 12-hour overnight fast.

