##### Possible covariables

2.6.2.3

Age, gender, and general medical history will be assessed at baseline. Participants will not be allowed to receive concomitant interventions, such as drugs affecting lipid metabolism, including lipid-lowering agents, weight loss medications, antihypertensive agents, and oriental medicines. Continuous use of functional foods and ingredients, such as omega-3 fatty acids, plant sterols, psyllium seed husk, aloe, and chitosan, will not be allowed during the duration of the study. During the study period, current medication and supplement use by the participants will be assessed during every visit.

Weight, waist circumference, and BMI will be measured during every visit. Height will be measured in the standing position without shoes, and weight will be measured using a weighing scale with minimal clothes. BMI will be calculated by dividing the weight (in kilograms) by the square of the height (in meters). Waist circumference will be then measured in the standing position, intermediate between the lower margin of the ribs and the iliac crest. We will use the same equipment during each visit and will take special care so that the same researcher can measure these parameters at the same time.

Dietary intake and lifestyle, including habitual physical activity, history of alcohol consumption, and smoking, will be investigated. Normal dietary intake patterns will be assessed using the Recommended Food Score.^[14]^ Background dietary intake, including total energy and macronutrient, will be assessed using 3-day food intake records by a mobile application. Three-day food intake records will be collected for 2 weekdays and 1 weekend day at baseline, 4, and 8 weeks after intervention to monitor dietary compliance. Physical activity will be evaluated during screening using the International Physical Activity Questionnaire (IPAQ, Korean version).^[15]^ During enrolment, habitual physical activity levels will be assessed at baseline and during follow-up visits. During the study period, the participants will be asked to maintain their usual diets, smoking habits, and physical activity and asked to avoid excessive antioxidant-containing foods, such as vegetables and fruits. In addition, participants will not be allowed to consume alcohol or perform vigorous physical activity for 48 hours before investigator visits.

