### Statistical analysis

2.7

Data analysis will be conducted by well-trained statisticians, not associated with the research team. Data will be examined for the presence of normality, outliers, violations, and/or missing data. A per-protocol analysis of the participants, who follow the protocol and complete the study, will be carried out. Baseline characteristics will be compared between groups using the Student *t* test. Continuous normally distributed variables will be compared between groups using analysis of covariance or linear mixed effect model. Pearson χ^2^ test or Fisher exact test will be used for categorical variables. For inter-group analysis, paired *t* test or Wilcoxon signed-rank test, will be performed for continuous variables. A *P*-value <.05 will be considered statistically significant. All analyses will be conducted using the SAS software. If needed, models will be adjusted for relevant confounding variables, and a stratified analysis will be performed.

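### Covariate adjustment rests on an undefined 'if needed' rule, and the between-group model is not committed to gender, the randomisation stratum

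*Protocol article*

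**What the plan says.** Section 2.4 of the protocol article allocates participants 1:1 and adds: "Randomization is stratified by gender".

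Section 2.7 gives the between-group method: "Continuous normally distributed variables will be compared between groups using analysis of covariance or linear mixed effect model". It does not choose between the two models or list a term for either. It closes with the covariate rule: "If needed, models will be adjusted for relevant confounding variables, and a stratified analysis will be performed". Need and relevance are not defined. Even if the second half of that sentence is read as unconditional, it does not say by which factor the analysis is stratified.

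The same section plans baseline tests: "Baseline characteristics will be compared between groups using the Student *t* test".

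The pool of candidates is wide. Section 2.6.2 says that "possible covariables, including demographic information, anthropometric measures, dietary habits, physical activity, alcohol consumption, and smoking behavior, will be assessed". Gender appears in section 2.6.2.3, under the heading for possible covariables: "Age, gender, and general medical history will be assessed at baseline". The abstract's conclusion presents the trial as "a randomized, double-blind, placebo-controlled trial that considers confounders, such as dietary habits, lifestyle factors, and genetic factors".

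**The concern.** When randomisation is stratified by a factor that predicts the outcome, the arms are forced to be alike on it, so the treatment estimate varies less than under simple randomisation. A model without that factor still counts its variance as noise. The standard error is then too large, the test is conservative and power is lost. Here the stratum is one optional covariate among many.

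The second issue is choice. If the decision to adjust, and for what, can be made after the outcome data are seen, the reported P-value no longer has its stated error rate. In a trial of 68 people with a long covariable list, several defensible models can give different answers, and the published rule does not say which one counts.

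**Working it through.** **1. The plan's own figure.** Section 2.6.4 gives 27 evaluable per group, 20% dropout, 80% power and two-sided alpha 0.05. 27 / (1 − 0.20) = 33.75, rounded up to 34 per group, 68 in total. This reproduces. The 27 cannot be rebuilt, because the article gives no LDL-C difference or SD. The standardised effect it implies is (1.96 + 0.84) × √(2/27) = 0.76 SD, which is used below.

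**2. Omitting the stratum.** Let R be the share of outcome variance explained by gender. R is an assumption, since the documents give no value. Put k = √(1 − R) and hold the total SD at 1. With gender exactly balanced across arms, the normal approximation gives:

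- type I error without gender: 2 × [1 − Φ(1.96 / k)]
- power without gender: Φ((2.80 − 1.96) / k)
- power with gender: Φ(2.80 / k − 1.96)

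| R | Type I error, gender omitted | Power, omitted | Power, included | Loss (points) |
|---|---|---|---|---|
| 0% | 5.0% | 80.0% | 80.0% | 0 |
| 5% | 4.4% | 80.6% | 82.0% | 1.4 |
| 10% | 3.9% | 81.2% | 84.0% | 2.7 |
| 20% | 2.8% | 82.7% | 87.9% | 5.3 |

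A simulation of the fitted linear models (20,000 replicates, 27 per arm, near-equal gender split) let the arms differ by one participant on gender, in the direction unfavourable to the product. At R = 5 / 10 / 20%:

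- Power without gender was 77.5 / 77.2 / 77.1%, against 80.6 / 82.7 / 86.7% with it: a loss of 3.1 / 5.5 / 9.6 points.
- Type I error without gender was 4.1 / 3.7 / 2.8%, against about 4.6% with it.

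The larger losses come from that one participant. The imbalance shifts the unadjusted estimate by (1/27) × 2√R, which is 0.033 SD at R = 20%. A re-run with exact balance (40,000 replicates) gave losses of 1.5 / 3.0 / 5.8 points. With the one-participant imbalance in the other direction, the loss was between none and about 2 points. So the loss is about 2 to 6 points under exact balance, and up to about 10 with a small unfavourable imbalance.

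**3. Choosing covariates freely.** Assume no treatment effect, 27 per arm and five candidate covariates, and report the smallest P-value found.

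- No covariates, each one singly, or all five (7 models), with covariates explaining 10 to 30% of variance in total: type I error 9 to 10%.
- All 2⁵ = 32 subsets, each coefficient 0.3, residual SD 1 (variance explained 0.45 / 1.45 = 31%): about 15%.
- All 32 subsets, total variance fixed at 1 (variance explained 5 × 0.3² = 45%): about 18 to 19%.

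**4. Baseline tests as a guide.** Under correct randomisation, the chance of at least one P < 0.05 is 1 − 0.95⁵ = 23% for five independent tests and 1 − 0.95¹⁰ = 40% for ten. Such tests would be a poor basis for choosing covariates.

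**The case against.** The strongest objection is that this is a condensed journal article, and that model terms are commonly left to a full protocol or SAP that is not shown. Silence on covariates would indeed be no finding. But section 2.7 is not silent: it states a rule, and the rule makes adjustment discretionary. An SAP that fixed gender and baseline LDL-C unconditionally would depart from that published rule.

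Three stronger readings are tempting, and the documents do not support them:

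- *The baseline t tests decide whether to adjust.* Section 2.7 contains both statements but does not connect them.
- *Gender is excluded and the analysis ignores the design.* Gender is a listed possible covariable, a stratified analysis is mentioned, and analysis of covariance implies at least one covariate, usually the baseline value. Gender is optional and unspecified, not ruled out.
- *On-treatment values will be adjusted for.* Section 2.6.2.3 does list repeated weight, diet and activity measures, but the purpose given for the food records is monitoring of dietary compliance. No section puts week 4 or week 8 values into an efficacy model.

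Two further points stand. Omitting a balanced stratum makes the test conservative; it does not create false positives. And blinding (section 2.4), together with statisticians from outside the research team (section 2.7), makes a deliberate search for the smallest P-value less likely. These safeguards lower the risk but do not define the model.

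**Conclusion.** The point holds in a limited form. The covariate rule has no criterion, and the model is not tied to the factor used to stratify randomisation. Two consequences are permitted by the text, not planned in it.

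First, if gender is left out and explains 5 to 20% of outcome variance, type I error falls to about 4% down to 3% and power drops by about 2 to 10 points, the upper end requiring a small unfavourable gender imbalance. Both effects vanish if gender is not prognostic.

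Second, covariates remain open to choice after the data are seen. The 9 to 19% type I error range bounds a deliberate search over five candidates; it depends on how many models are tried and how strong the covariates are, and it does not predict what these analysts will do.

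This should be corrected because the correction is free. It does not invalidate the design.

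**What to change.** Replace the conditional sentence in section 2.7 with one fixed primary model for LDL-C containing treatment, baseline LDL-C and gender, plus visit and treatment-by-visit terms if the mixed model is used. Report any further adjustment only as a sensitivity analysis, on a short set of baseline variables listed before unblinding. State that neither baseline significance tests nor values measured after randomisation will be used to choose or form covariates in the efficacy model; baseline characteristics can be presented descriptively.

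The cost is wording only. Section 2.6.2.1 already has the lipid profile measured at baseline, and section 2.6.2.3 already records gender. Sample size, visits and data collection do not change.

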### Data collection and quality control

2.8

Data in this study will be compiled using the electronic case report forms. After every visit is completed at hospital, data will be entered using the electronic case report system. This study will be monitored by BiofoodCRO Co, Ltd (Seoul, South Korea). Periodic monitoring will allow high accuracy and quality throughout the study.

## Results

3

A consort diagram is described in Figure 2.

**Figure 2 F2:**
[figure not shown]
Consort diagram.

## Discussion

4

To our knowledge, this is the first randomized, double-blind study to investigate the cholesterol-lowering effects of yellow yeast rice. We hope that the results of this study will provide scientific evidence on the effectiveness of yellow yeast rice against mild to moderate hypercholesterolemia in adult patients. To facilitate appropriate high-quality methodology and strict quality control, this protocol has been developed according to the CONSORT statement.^[16]^
